## Abstract

**Background:**

Adolescents with intellectual disabilities have an increased risk of developing academic, social, and psychological problems compared with non-disabled peers. These difficulties might have an impact on the implicit theories—or so called mindset—of these youth. Youth with a fixed mindset believe that their attributes are static while youth with a growth mindset believe their attributes are malleable. A growth mindset can positively affect the academic and psychosocial development of youth and can be stimulated by so called ‘mindset interventions’. Nevertheless, mindset interventions specifically adapted to adolescents with intellectual disabilities are non-existing.

**Methods/design:**

The aim of the present study is to conduct a randomized controlled trial (RCT) to test the effectiveness of the online mindset intervention “The Growth Factory” aimed to teach adolescents with intellectual disabilities a growth mindset and thereby positively impacting their psychosocial development. The RCT targets adolescents (12–23 years) with mild to borderline intellectual disabilities (IQ 50–85) admitted to residential care or special education. Participants will be individually randomized to the intervention (*n* = 60) or control (*n* = 60) group. The intervention group will individually participate in the six sessions of “The Growth Factory” and the control group will receive care as usual. Primary outcome will be mindset. Empowerment, behavior problems, self-esteem, treatment motivation, therapeutic alliance, challenge seeking, and the impact of social exclusion will be included as secondary outcome measures. Moreover, moderation (i.e., intervention satisfaction, IQ, age, baseline mindset, gender) and mediation effects will be investigated. Self-reported and mentor assessments will be administrated at baseline, post-test and at three (except mentor assessment) and six months follow-up.

**Discussion:**

This paper describes the design of a RCT examining the effectiveness of the online mindset intervention “The Growth Factory” aimed to empower adolescents with intellectual disabilities. If effective, “The Growth Factory” makes an important contribution to the treatment and psychosocial development of adolescents with intellectual disabilities in residential care and special education. Due to the online approach, implementation will be efficient and cost-effective and therefore the intervention “The Growth Factory” can be used on large scale.

**Trial registration:**

Dutch Trial Register NTR5460. Registered 2 October 2015.

## Background

Youth with intellectual disabilities are highly vulnerable and experience more difficulties and delays in academic, social, and adaptive skills [1–4]. In addition, research shows that young people with intellectual disabilities have an increased risk of developing emotional and behavioral problems [2–9]. Youth with intellectual disabilities show more externalizing problems, such as attention problems and aggressive behavior, than their non-disabled peers [2, 5–7]. The same holds for internalizing problems, such as depression and anxiety [2, 3, 5–7, 10, 11]. Moreover, youth with intellectual disabilities often suffer from overprotective care [12–14]. Due to their disabilities, many youth with intellectual disabilities are restricted by caregivers’ low expectations and fear for their safety [14]. Overprotective care may hamper identity building, independence and autonomy in youth with intellectual disabilities, and is related to psychosocial maladjustments [12–14].

The experience of academic and psychosocial problems, amongst other factors, might have an impact on the implicit theories of youth with intellectual disabilities. Implicit theories—also referred to as mindset—are core assumptions about the malleability and controllability of particular attributes such as intelligence, emotion, behavior, and personality [15, 16]. These implicit theories create a framework for interpreting the meaning of events in one’s world. Two types of mindsets can be distinguished, that is a fixed mindset (an entity view) and a growth mindset (an incremental view).

In particular, youth with a fixed mindset consider attributes such as intelligence and personality to be static and unchangeable. For example, they might believe that people have certain personality traits that cannot be altered [15]. For this reason, effort is seen as useless and hard work will be without results or success. Furthermore, youth with a fixed mindset will tend to avoid challenging situations and will see setbacks as threatening and self-defining because it indicates a general lack of ability [15, 16]. As a result, people endorsing a fixed mindset may not achieve their full potential. In contrast, people with a growth mindset believe people’s characteristics have the potential to change and see these attributes to be dynamic. For example, they may believe that everyone can take steps to develop their personality and behavior over time [15]. For this reason, those who believe these attributes are malleable tend to engage in behaviors that will help them to develop their abilities, such as expanding effort to improve and embrace challenges as opportunities to grow [15, 16]. As a result, youth with a growth mindset intend to use their full potential and therefore might reach higher levels of academic achievement and psychosocial functioning [16–18]. The present study focuses specifically on the impact of a growth mindset on enhancing the psychosocial development of youth with intellectual disabilities.

Indeed, an extensive amount of research has shown significant associations between mindsets and a wide range of psychological outcomes [17–23]. The psychological constructs in the present study to assess effectiveness outcomes of the intervention will be discussed. Research has shown that a growth mindset is associated with psychological empowerment [19]. Empowerment is the experienced personal competence and perceived control to handle important matters [24–26]. In addition, the belief in the malleability of one’s own capabilities impacts one’s self-regulation of behavior and motivation [17, 19, 26–28]. For example, people with a growth mindset set goals focused on learning to increase their ability [17, 27, 28] as they are more likely to prefer challenging activities compared to people with a fixed mindset [20]. Furthermore, people with a growth mindset employ mastery-oriented strategies by displaying more willingness to work hard and persistently, even when faced with adversity, to reach their goals [17, 28–30]. Consequently, people endorsing a growth mindset are more likely to be confident in successfully making a change and therefore more likely to be motivated for treatment (i.e., treatment readiness) to improve their emotions and behavior [21, 29]. Subsequently, a growth mindset might also be related to building positive therapeutic relationships [22, 30, 31]. For example, people who have a growth mindset believe in personal responsibility for working hard and achieving progress and therefore are more likely to evaluate their relationship with their counselor as collaborative and productive than people with a fixed mindset [30]. In addition, a growth mindset is related to lower levels of internalizing and externalizing problems, such as anxiety, depression, and aggressive behavior [18, 32–34]. Moreover, mindsets are associated with (long-term change in) self-esteem, with people with a fixed mindset showing lower levels of self-esteem and a downward spiral in self-esteem levels in response to new (academic) challenges compared to those with a growth mindset [17, 34]. Finally, mindsets are related to people’s social relationships [23, 35–38]. Specifically, a fixed mindset has been related to a greater desire for vengeance when adolescents recalled recent conflicts in their lives [23]. Moreover, children with a fixed mindset are more likely to demonstrate internalizing and externalizing health problems when victimized [37, 38].

In sum, a growth mindset can positively impact adolescents’ academic, social, and psychological development. Therefore, so called ‘mindset interventions’ have been developed to teach children and adolescents a growth mindset. Mindset interventions are brief psychological interventions based upon the previously described scientific research concerning implicit theories of intelligence and personality [39]. A key message of mindset interventions is that attributes are malleable and can be changed. Thus, these interventions show the plasticity of the brain and the impact of effort and practice. Furthermore, the focus of these mindset interventions is on implicit and unconscious beliefs instead of teaching new skills or behavior [39]. Mindset interventions are generally one to eight sessions long and are executed face-to-face or using a computer program using an individual or group format.

Interestingly, mindset interventions have been shown to be successful in stimulating a growth mindset and subsequently positively impacting adolescents’ academic performance and psychosocial functioning [27, 37, 39–43]. First, mindset interventions showed the predicted effect of increasing a growth mindset in adolescents [19, 37, 41, 44, 45]. Second, mindset interventions significantly increased feelings of empowerment in youth [19]. Third, previous research found that after a short growth mindset manipulation youth were more willing to take on challenges compared to youth who received a fixed manipulation [20, 43]. Fourth, providing youth with conduct problem and psychopathic features with an intervention including a growth mindset component demonstrated increased positive emotion and improvement in treatment amenability (i.e., awareness of problems, motivation to change, and consideration and tolerance of others) [42]. Fifth, mindset interventions can make an important contribution to the prevention and reduction of behavioral problems [41, 44]. In particular, a brief mindset intervention teaching adolescents that people can change prevented internalizing problems (e.g., symptoms of depression) [41] and externalizing problems (e.g., aggression) [39]. Sixth, a single session intervention teaching a growth mindset of personality was effective in preventing a decline in self-esteem [41]. Finally, mindset interventions had a positive impact on social relationships [23, 39]. For example, youth who have participated in a mindset intervention responded less aggressive and more prosocial in reaction to social rejection compared to youth in the control group [39].

Despite these impressive findings, previous mindset research has been mainly conducted in educational settings with adolescents without disabilities. However, according to a few studies, children and adolescents with intellectual disabilities are more likely to endorse a fixed mindset than peers without disabilities [43, 46, 47]. Furthermore, research shows that a growth mindset is related to higher levels of empowerment and self-esteem in youth with intellectual disabilities [46]. Also, higher levels of a growth mindset are related to lower levels of internalizing problems, attention problems, externalizing problems, and total behavior problems [46] and are not associated with challenge avoidance [43, 47]. These results suggest that teaching a growth mindset might make a significant contribution to the development of youth with intellectual disabilities. However, mindset interventions adapted to the needs of adolescents with intellectual disabilities are lacking. Therefore, we developed a brief six session online mindset intervention “The Growth Factory” aimed to teach youth with intellectual disabilities a growth mindset.

In a randomized controlled pilot study (*n* = 59) we showed that it was feasible to implement the online intervention in practice and that the majority of adolescents with psychiatric problems often combined with intellectual disabilities evaluated “The Growth Factory 1.0” positively [48]. The pilot study also demonstrated that the intervention significantly increased a growth mindset and feelings of empowerment of adolescents with intellectual disabilities and/or psychiatric problems in comparison with a control group—although the intervention did not show the expected beneficial downstream effects on internalizing problems, externalizing problems, and self-esteem. Based on these findings, and on participant and trainer evaluations in the pilot study, “The Growth Factory 1.0” was further improved into “The Growth Factory 2.0”—in this article further referred to as “The Growth Factory”—to increase the effectiveness of the intervention for adolescents with intellectual disabilities. Some important changes were the correction of technical errors, the addition of a participant workbook, and the addition of two assignments on the relationship between cognitions and behavior.

The primary aim of the present study therefore is to examine the effectiveness of the online intervention “The Growth Factory” using a full scale randomized controlled trial (RCT) with four measurement moments. “The Growth Factory” aims to empower youth with intellectual disabilities by stimulating the development of a growth mindset and thereby positively impacting their psychosocial development. We hypothesize that adolescents in the intervention group will show larger increases in growth mindset (primary outcome). Furthermore, we hypothesize that adolescents in the intervention group will show greater improvements in empowerment, self-esteem, treatment motivation, and therapeutic alliance as well as a larger reduction of internalizing problems, attention problems, externalizing problems, and total behavior problems compared with adolescents in the control group (secondary outcomes). Finally, we hypothesize that adolescents in the intervention group will seek challenges more and will be less negatively impacted by social exclusion compared with adolescents in the control group (secondary outcomes). In addition, the secondary aim of this study is to gain insight for whom the intervention “The Growth Factory” is effective (i.e., moderation) and how the intervention works (i.e., mediation). Intervention satisfaction, level of intellectual disability (mild intellectual disability versus borderline intellectual functioning), and baseline mindset will be tested as moderators of the effects of the online mindset intervention. We hypothesize that adolescents with higher intervention satisfaction scores, borderline intellectual functioning, and a fixed mindset at baseline will show larger increases in growth mindset compared to adolescents with mild intellectual disabilities, who report less satisfaction with the intervention, and a more growth oriented mindset at baseline. In addition, we will explore whether age and gender moderate the intervention effect. Finally, we will test the mediating role of mindset on the effect of the mindset intervention on the secondary outcomes measures.

## Methods

The study design will be reported in accordance with the CONSORT 2010 statement for reporting parallel group randomized trials [49]. The Ethics Committee of the University of Amsterdam in the Netherlands has approved the study (2015-CDE-4518). Moreover, the study is registered in the Dutch Trial Register for RCT’s (NTR5460).

### Design

The present study involves a randomized controlled trial with two conditions: an intervention group and a control group with four measurements at pre-test, post-test, follow-up at 3 months and 6 months. Figure 1 shows a schematic overview of the design in the present study.

**Fig. 1 Fig1:**
[figure not shown]
Study design. Flow diagram of recruitment, inclusion and exclusion criteria, randomization and different assessments

### Participants

Participants that will be selected for the study are (late) adolescents (12 to 23 years) with mild to borderline intellectual disabilities, including youth with mild intellectual disabilities (IQ 50–69) and borderline intellectual functioning (IQ 70–85) and deficits in adaptive functioning. Besides an intellectual disability participants could have accompanying physical disabilities or psychiatric problems. Participants are clients in residential care or students in special education. Exclusion criteria are the presence of severe emotional problems hindering participation in the study, such as extreme aggression problems or an acute unstable mental condition. Participants who agree to participate will be included in the study when both adolescent and parents or legal representative provide written informed consent.

A power analysis [50] was performed to calculate the sample size required in the present study. Based on previous research on the effectiveness of mindset interventions in education [39], the expectation is to find a small to medium effect (*d* = 0.25). The power calculation (two-tailed, alpha 0.05, statistic power 0.80) based on a three measurements design shows that 106 participants are necessary. Therefore, our aim is to include *N* = 120 participants (*n* = 60 intervention group; *n* = 60 control group) in the RCT taking into consideration 10% attrition.

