### Statistical analyses

Following the intention-to-treat principle, the data from all participants randomized to either the intervention or control group will be analysed. Multiple imputations will be used for missing values at post-intervention and follow-up measurements. In addition, a completers only analysis will be conducted (i.e., participants that completed five or six sessions). The results will be reported in accordance with the CONSORT Statement [49].

Possible baseline differences between the two groups in background variables (e.g., age, gender) and relevant study variables will be examined using independent-sample t-tests. In case of differences at baseline, variables will be included as covariates in all models testing the effectiveness of the intervention. Furthermore, the effectiveness of the intervention will be analysed using repeated measures ANOVA for differences within subjects (i.e., pre-test, post-test, follow-up 1, and follow-up 2 measurements) and between subjects (intervention versus control group). In addition, intervention satisfaction, level of intellectual disability, age, baseline mindset, and gender will be tested as moderators of the effects of the online mindset intervention.

These moderator effects will be tested using three-way interactions in our repeated measures design. The effect of the mindset intervention on the secondary outcomes measures, (i.e., empowerment, internalizing problems, attention problems, externalizing problems, and total behavior problems, self-esteem, treatment motivation, therapeutic alliance, challenge seeking, and impact of social exclusion) might be mediated by mindset. This will be tested in several mediation analyses in Mplus [68].

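### The 80% power claimed at d = 0.25 with 106 participants rests on an effect-size conversion that does not fit the group-by-time test; at a correlation of 0.5 the calculation is in effect sized for a sustained difference of about 0.53 SD

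*Protocol article*

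**What the plan says.** All in the Protocol article:

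- **Participants (effect size):** drawing on earlier research on mindset interventions in education, "the expectation is to find a small to medium effect", given as d = 0.25.
- **Participants (sample size):** "The power calculation (two-tailed, alpha 0.05, statistic power 0.80) based on a three measurements design shows that 106 participants are necessary". The target is then raised to 120 (60 per arm) to allow for 10% attrition.
- **Design:** the trial has "four measurements at pre-test, post-test, follow-up at 3 months and 6 months". The aims in Background also describe a trial "using a full scale randomized controlled trial (RCT) with four measurement moments".
- **Statistical analyses:** effectiveness is tested by repeated measures ANOVA, with a between-group factor and "differences within subjects (i.e., pre-test, post-test, follow-up 1, and follow-up 2 measurements".
- **Background (primary hypothesis):** growth mindset is expected to increase more in the intervention group than in the control group. In a repeated measures ANOVA that is the group-by-time interaction.

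The sample-size paragraph does not give the correlation between repeated measurements, which ANOVA effect was powered, or how d was turned into the effect size f that such a calculation needs.

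**The concern.** An ordinary two-group comparison of means at d = 0.25 needs about 252 per arm (504 in total) for 80% power. Repeated measurement can reduce that number, but a fall to 106 needs an explanation, and the paragraph gives none.

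The trial presents itself as full scale and sized for the effect it expects. If its power at that effect is well below 80%, a null result on the primary outcome could be read as evidence against a small-to-medium effect that the planned test would often miss. The number of measurements behind the calculation (three) also differs from the number analysed (four).

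**Working it through.** **Inputs from the article.** d = 0.25; two-sided alpha 0.05; power 0.80; three measurements in the calculation and four in the design and analysis; two equal arms; 120 randomised; 10% attrition, so 120 × 0.9 = 108 analysable.

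**Assumptions of mine.** The within-person correlation r is not in the article; it is set at 0.5 to reproduce the plan's figure and then varied from 0.3 to 0.8. Sphericity is assumed. The effect pattern is no difference at T0 and a constant difference d (in SD units) at every later occasion.

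**Formula.** For a group-by-time interaction with two groups, m occasions and N participants in total, the test is a noncentral F with λ = f²·N·m/(1 − r), df1 = m − 1 and df2 = (N − 2)(m − 1).

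**Step 1: reproduce 106.** Take f = d/2 = 0.125, m = 3, r = 0.5. At N = 106, λ = 0.015625 × 106 × 3/0.5 = 9.94, with df 2 and 208.

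| N | Power |
|---|---|
| 104 | 0.799 |
| 105 | 0.803 |
| 106 | 0.807 |

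The smallest N is 105, or 106 with equal arms. Other routes tried at r = 0.5 do not give 106: between-subjects main effect with f = 0.125, N = 337; the same with f = 0.25, N = 86; interaction with f = 0.25, N = 28; interaction with f = 0.125 and four occasions, N = 89.

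The attrition step is sound: 106/0.9 = 117.8, rounded up to 118, and 120 are planned.

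**Step 2: what f means in this test.** Here f is the root mean square of half the time-centred group differences.

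- Three occasions, differences (0, d, d): the mean is 2d/3 and the deviations are −2d/3, d/3, d/3. Their mean square is (4 + 1 + 1)d²/27 = 0.2222d², with root 0.4714d. Half of that is f = 0.236d.
- Four occasions, differences (0, d, d, d): the mean is 3d/4 and the deviations are −3d/4 and three of d/4. Their mean square is (9 + 3)d²/64 = 0.1875d², with root 0.4330d. Half of that is f = 0.217d.

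At d = 0.25 this gives f = 0.059 (three occasions) or 0.054 (four), not 0.125. Conversely, in the plan's own three-occasion calculation, f = 0.125 corresponds to d = 0.125/0.2357 = 0.53.

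**Step 3: power for the trial as designed.** N = 108, m = 4, sustained effect. Example at r = 0.5: f² = (0.2165 × 0.25)² = 0.00293, λ = 0.00293 × 108 × 4/0.5 = 2.53, power 0.233.

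| r (assumed) | Power at d = 0.25 | d detectable with 80% power |
|---|---|---|
| 0.3 | 0.175 | 0.62 |
| 0.5 | 0.233 | 0.52 |
| 0.7 | 0.372 | 0.40 |
| 0.8 | 0.537 | 0.33 |

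Solving for r, 80% power at d = 0.25 needs r of about 0.885 at N = 108 (about 0.887 at N = 106).

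**Step 4: three versus four occasions.** At N = 108, r = 0.5 and d = 0.25, power is 0.246 with three occasions and 0.233 with four, so this mismatch changes little.

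**Step 5: another effect pattern.** If the difference builds up linearly to d at T3 instead of being sustained, power at r = 0.5, N = 108 and four occasions is 0.180.

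**The case against.** The strongest reply is that nothing has been miscalculated. The number 106 comes out under a common software convention, and if d was meant as 2f on the interaction scale, 80% is correct as computed. That the arithmetic reproduces is true, and a reader who inferred an arithmetic slip would go too far. But the paragraph takes d from earlier intervention research, calls it small to medium and gives no special definition, so it will be read as an ordinary between-group difference. On the 2f reading, at r = 0.5, the trial is powered for a sustained difference above half an SD, and the text does not say so.

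The second reply is that r is not reported and that such settings are often left to a full protocol. This stands in part. A reader might infer that power is simply 25% and that 80% is reached only near d = 0.5. The documents do not support that as an unconditional statement, because both figures belong to r = 0.5 with a sustained effect. Nor do they show that 106 can be reached only by the route in Step 1. With the conversion in Step 2, 80% power at N = 106 also arises at r of about 0.887, and a between-subjects test with f = 0.25 gives about 106 at r near 0.74. That last route treats 0.25 as f, which means d = 0.5, so it does not rescue the label. The route through f = d/2 and r = 0.5 is therefore a well-fitting inference about the settings, not something the article states.

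What the reply does not remove is the range. For r from 0.3 to 0.8, power at d = 0.25 stays well below 80%. A correlation near 0.89 among all occasions up to the six-month follow-up is hard to square with the article's own modest description of the reliability of the Mindset Questionnaire subscales.

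**Conclusion.** The concern holds as a fault in converting or labelling the effect size. If d = 0.25 is a standardised between-group difference, zero at baseline and sustained afterwards, the planned group-by-time test does not have 80% power with the planned numbers unless r is about 0.885 or more. Across r from 0.3 to 0.8 the shortfall is large: between about 18% and 54% power instead of 80%, and a detectable difference between about 0.62 and 0.33 SD instead of 0.25.

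The figures rest on 108 analysable participants, four occasions, sphericity and an r that no document supplies. The finding that f = d/2 is the wrong conversion for a sustained effect in this test does not depend on r. The three-versus-four mismatch is real but minor, and the attrition allowance is adequate.

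**What to change.** Keep N at 120 and rewrite the sample-size paragraph so that it:

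1. uses the four occasions that are analysed;
2. defines d as the between-group difference in SD units and states the assumed pattern over time;
3. names the effect tested (group-by-time), the d-to-f conversion and the assumed r with its source;
4. replaces the claim of 80% power at d = 0.25 with the detectable difference and the power at d = 0.25 over a range of r.

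Possible wording: *With 108 analysable participants, four occasions, sphericity and a between-group difference that is zero at baseline and constant afterwards, the group-by-time test has 80% power for a difference of about 0.62, 0.52, 0.40 or 0.33 SD if the within-person correlation is 0.3, 0.5, 0.7 or 0.8; its power at 0.25 SD is then about 18%, 23%, 37% or 54%.*

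No single correlation should be written in as fact unless the sponsor can support it, for example from the trial's own pilot data.

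The cost is wording only, with no extra participants and no change to the analysis. The downside is that the stated sensitivity becomes less favourable, and a null result will have to be reported as leaving a difference of 0.25 SD open.
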